### Usual care group

Participants in the usual care group receive usual care and are requested to maintain their habitual physical activity pattern.

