### Study outcomes

Table 2 summarizes the outcomes measured in the PERFECT study. All questionnaire outcomes, diaries and the accelerometers are assessed at baseline, post-intervention (12 weeks post-baseline) and 24 weeks post-baseline. At baseline and post-intervention these outcomes are assessed during a study center visit. At 24-weeks participants receive the questionnaires by mail. Physical fitness and blood markers are assessed at baseline and post-intervention. Recurrence and survival will be assessed 2- and 5-year post-diagnosis. Socio-demographic data (age, sex, education, marital status) and smoking status are assessed at baseline with a self-developed questionnaire. Medical data (diagnosis, tumor type, disease stage, type of treatment, and comorbidities) are retrieved from medical records. Personal data are coded and all data are handled by the researchers in compliance with the Dutch Personal Data Protection Act. The PERFECT study is checked on safety for participants and validity of data by an independent monitor.

**Table 2 Tab2:** Study outcomes

Outcomes	Instrument	Baseline	12-week	24-week
Primary outcome				
Quality of life	EORTC-QLQ-C30	X	X	X
Secondary outcomes				
Esophageal cancer specific symptoms	EORTC-QLQ-OG25	X	X	X
Fatigue	Multidimensional Fatigue Inventory (MFI)	X	X	X
Anxiety and depression	Hospital Anxiety and Depression Scale (HADS)	X	X	X
Sleep quality	Pittsburgh Sleep Quality Index (PSQI)	X	X	X
Work-related factors	iMTA Productivity Cost Questionnaire (iPCQ)	X	X	X
Cardiorespiratory fitness	Cardiopulmonary exercise testing (CPET)	X	X	
Muscle strength	MicroFET handheld dynamometer	X	X	
Physical activity	Short questionnaire to assess health enhancing physical activity (SQUASH)	X	X	X
	ActiGraph accelerometer	X	X	X
	Exercise log		X	
Malnutrition risk	Patient-Generated Subjective Global Assessment Short Form (PG-SGA SF)	X	X	X
Dietary intake	3-Day food diary	X	X	X
Anthropometry	Body weight, height, BMI, waist and hip circumference	X	X	
Blood parameters	Serum, plasma and cell pellet	X	X	
Adherence and compliance	Registration in case report form, exercise log	X	X	
Recurrence and survival	Medical records and Dutch Cancer Registry			
Other				
Sociodemographic data	Self-developed questionnaire	X		
Medical data	Medical records	X		
Adverse events	Reports of patients, physiotherapists, oncology nurses, physicians, medical records	X	X	X

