#### Physical activity

Physical activity behavior is assessed using the short questionnaire to assess health enhancing physical activity (SQUASH), which includes items on commuting activities, leisure time activities, household activities, and activities at work and school [30].

To assess physical activities (duration/intensity) and duration of sedentary behavior objectively, all participants wear an accelerometer (GT3X+ Tri-Axis Actigraphy Monitor, ActiGraph®) for seven consecutive days at baseline and follow-up measurements. In addition, participants in the intervention group are asked to keep an exercise log during the exercise program. In this exercise log, they document their daily activities.

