#### Adherence

Adherence incorporates both attendance at the supervised exercise sessions and compliance (i.e., performing the exercises according to exercise protocol). To monitor attendance, the physiotherapist documents presence of each participant at each session in a case report form. Furthermore, to monitor compliance, achieved heart rates and duration for the aerobic exercise components are documented, and weight and number of repetitions performed for the resistance components. In case of missed exercise sessions or non-compliance to the protocol, reasons are documented. At least every 4 weeks, this documentation is sent to the researchers for monitoring. Moreover, each physiotherapist is visited at least once by a member of the PERFECT study team, to ensure proper performance of the exercise protocol.

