### Statistical analysis

Descriptive statistics will be used to describe the study population and study parameters at baseline. Questionnaire scores (e.g. HRQoL and fatigue) will be calculated according to published scoring algorithms. Analyses will be performed according to the intention-to-treat principle. For the primary analysis mixed linear regression models will be used to model the HRQoL outcome measures at 12 and 24 weeks. The models will be adjusted for baseline HRQoL as well as for stratification factors. In these longitudinal analyses, the program accounts for missing data based on the observed data [37]. The same analyses will be performed for the secondary outcome measures. Secondary outcomes, which will only be assessed at baseline and 12 weeks (e.g. VO_2peak_), will be analyzed as between-group differences in outcomes using ANCOVA, adjusted for baseline and stratification factors. Cancer recurrence and survival will be analyzed using a Cox proportional hazards regression model. As an explorative analysis, attendance and compliance, sex, subtype of carcinoma, type of surgery and time since surgery will be examined as potential modifiers of the intervention effects. Furthermore, to adjust for treatment contamination, an instrumental variable analysis will be performed with treatment assignment as instrument and adjustment of the results for adherence [38].

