Second, effects of the exercise program might be influenced by so-called contamination (non-compliance) of the usual care group. This phenomenon is reported to occur in 37% of exercise-oncology trials and is caused by the fact that patients who participate in these type of trials are often highly motivated to exercise, which subsequently leads to an increase of physical activity levels, not only in patients randomized to the intervention group, but also in those randomized to the usual care group [40]. To prevent contamination, we include physically inactive patients (i.e., they might have less natural preference to adapt high physical activity levels when randomized to usual care), elaborate on the randomized design during the informed consent procedure in order to avoid disappointment when being randomized to the usual care group, and repeatedly stress the importance of the usual care group during the inclusion period. After completion of the trial, patients who were randomized to the usual care group can ask the study team for an exercise advice.

In conclusion, the PERFECT study is the first study to investigate effects of an exercise program in esophageal cancer patients after surgery. As the design closely resembles daily practice, results of this study can contribute both to evidence on effects of exercise in esophageal cancer patients, and potential implementation strategies.

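### The instrumental-variable analysis is meant to adjust for control-arm contamination, but the variable it names, adherence, is defined only for the exercise arm

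*Protocol article*

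**What the plan says.** The last sentence of the Statistical analysis section adds a supplementary analysis: "to adjust for treatment contamination, an instrumental variable analysis will be performed with treatment assignment as instrument and adjustment of the results for adherence". It gives a purpose (contamination), an instrument (randomised assignment) and one further variable (adherence). It does not define adherence.

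The definition is in the Adherence section: "Adherence incorporates both attendance at the supervised exercise sessions and compliance (i.e., performing the exercises according to exercise protocol". For attendance, "the physiotherapist documents presence of each participant at each session in a case report form". Table 2 under Study outcomes gives the data source for adherence as "Registration in case report form, exercise log". The Physical activity section says who fills in that log: "participants in the intervention group are asked to keep an exercise log during the exercise program".

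The Discussion deals with adherence and contamination as two separate threats. The first is poor adherence in the intervention group. The second is "so-called contamination (non-compliance) of the usual care group", explained as rising activity among patients who were not allocated to exercise. The Usual care group section gives that arm its only instruction: "Participants in the usual care group receive usual care and are requested to maintain their habitual physical activity pattern".

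Activity itself is measured in both arms: "all participants wear an accelerometer (GT3X+ Tri-Axis Actigraphy Monitor, ActiGraph®) for seven consecutive days at baseline and follow-up measurements". Table 2 schedules both the accelerometer and the SQUASH questionnaire at baseline, 12 and 24 weeks, with no restriction to one arm. The analysis sentence does not refer to either.

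**The concern.** An instrumental-variable estimate divides the intention-to-treat difference by the difference in exposure between the arms. To remove dilution from controls who take up exercise, the exposure has to register their exercise. Adherence, as the article defines it, does not: usual-care patients have no supervised sessions and keep no log.

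An analyst who followed the text would therefore correct for one kind of dilution (exercise-arm patients who do not train) and report the result as corrected for the other (controls who do). At stake is the interpretation of one secondary estimate. It could be read as the effect of exercising with contamination removed while contamination is still in it.

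**Working it through.** The article states no figure for this analysis, so there is nothing of its own to reproduce. The check compares the estimator under the two possible exposures.

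**Inputs**
- Δ, the effect of exercising: 9.0 points. This is the between-group difference in the earlier trial quoted under Sample size (15.1 − 6.1 = 9.0). It only sets the scale; the proportional result does not depend on it.
- a, the share of the exercise arm that adheres: assumed 80%, with 70% and 90% as a range.
- c, the share of controls who exercise: assumed 0 to 30%. The 37% in the Discussion is a share of trials that report contamination, not of patients, so it cannot serve as c.
- Further assumptions: exposure is yes/no and measured without error, and a control's own exercise has the same effect as the programme.
- Adherence is taken as the exposure in the model, because it is the only candidate the sentence names.

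**Formulas**
1. Intention-to-treat difference: Δ × (a − c).
2. Exposure is adherence as defined, so controls are all zero. The denominator is a − 0 = a, and the estimate is Δ × (a − c)/a.
3. Proportional shortfall: 1 − (a − c)/a = c/a.
4. Exposure measured in both arms. The denominator is a − c, and the estimate is Δ × (a − c)/(a − c) = Δ.

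**Results, in points**

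| a | c | ITT | IV, adherence as defined | Shortfall c/a |
|---|---|---|---|---|
| 0.8 | 0 | 7.2 | 9.0 | 0% |
| 0.8 | 0.1 | 6.3 | 7.9 | 12.5% |
| 0.8 | 0.2 | 5.4 | 6.75 | 25% |
| 0.8 | 0.3 | 4.5 | 5.6 | 37.5% |
| 0.7 | 0.3 | 3.6 | 5.1 | 43% |
| 0.9 | 0.3 | 5.4 | 6.0 | 33% |

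Worked line for a = 0.8 and c = 0.2: ITT = 9 × 0.6 = 5.4; IV = 5.4/0.8 = 6.75; shortfall = 0.2/0.8 = 25%. With an exposure measured in both arms, 5.4/0.6 = 9.0.

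A simulation of 2,000,000 patients with an unmeasured confounder, at 80% versus 20% exercising, gave 5.38 (ITT), 6.73 (IV on adherence) and 8.97 (IV on a both-arm exposure), in line with the formulas.

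**If the equal-effect assumption fails.** Suppose a control's own exercise delivers only a fraction k of the programme's effect. The ITT difference is then Δ(a − kc), and the adherence-based shortfall is kc/a, which is smaller. The both-arm estimate becomes Δ(a − kc)/(a − c), which exceeds Δ when k < 1. So the both-arm analysis returns 9.0 only under the assumptions listed.

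**The case against.** A reader might infer that this trial cannot correct for contamination. The article does not support that. Activity is measured in both arms with an accelerometer and a questionnaire, so the analysis is feasible. The article also calls contamination a form of non-compliance by the usual care group, and that group has an instruction to comply with, so a two-arm meaning of adherence is conceivable. It is not the natural reading: the Adherence section and Table 2 tie the term to session records and the log, and the Discussion keeps adherence and contamination apart.

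It is also fair to say that a condensed article leaves the operational exposure to the full analysis plan, which is not shown. That covers thresholds and model details. It does not cover a variable that the article names and defines in a way that does not fit the purpose it states.

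Another tempting inference is that the trial's effect will be understated by some definite percentage. That does not stand either. The values of a and c are assumptions, and 9.0 is a difference observed in an earlier trial, not an effect of exercising free of non-adherence and contamination. An estimate based on programme adherence is also a legitimate quantity: the effect of the programme in those who follow it, against usual care as it occurs. The fault is in calling that contamination-adjusted.

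Finally, a both-arm activity measure has weaknesses of its own. The programme also delivers resistance training, physiotherapist contact and goal-setting. Benefit through those routes would be credited to activity minutes, so the exclusion restriction is doubtful and the estimate could be too high. This objection stands and has to be stated with the fix.

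**Conclusion.** The point holds as a mismatch between the analysis's stated purpose and the variable it names. With adherence as the article defines it, control exposure is zero, non-adherence in the exercise arm is corrected, and contamination leaves a proportional dilution of c/a. For illustration this is 25% at a = 80% and c = 20%, if controls' exercise works as well as the programme; it is smaller if their exercise works less well, and zero if no control exercises.

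Severity is low. The analysis is supplementary, the primary intention-to-treat analysis and the sample size are untouched, and the data needed for a better exposure are already planned.

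**What to change.** Before analysis, choose one of two wordings.

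1. Name as the exposure one activity measure taken identically in both arms: moderate-to-vigorous activity at 12 weeks from the accelerometer or SQUASH, preferably kept continuous. Use assignment as the instrument and adjust for baseline HRQoL, baseline activity and the stratification factors. Keep adherence, as the article defines it, for describing the exercise arm.
2. Keep the adherence-based analysis, but report it as adjusted for non-adherence in the exercise arm only, not for contamination.

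Under the first option, state the limits: a seven-day or self-reported measure at 12 weeks is noisy and reflects the end of the programme rather than its whole course, and the exclusion restriction is doubtful because of the programme's other components, so the estimate could be too high.

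The cost is a change of wording. No new data are needed. The exposure should be fixed before results are seen, since a later choice would weaken the estimate.

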## Discussion

The aim of the PERFECT study is to investigate effects of exercise on HRQoL in esophageal cancer patients after surgery. Results of exercise on HRQoL in other types of cancer are promising, however effects in esophageal cancer patients have not been assessed before.

A special feature of the current study is the supervision of the exercise program by physiotherapists near the home-address of the participants who are randomized to the intervention group. As this approach diminishes travel burden considerably, we expect it to improve adherence of the participants. It might be challenging though, as for each individual participant an appropriate physiotherapist needs to be identified and trained, directly after randomization into the intervention group. However, as the Dutch (oncology) physiotherapy community is an expanding and highly motivated group of health care professionals, we expect this procedure to be feasible. Moreover, since this approach strongly resembles the real world situation, results of the study will be well generalizable and, as a consequence of developing a network of trained physiotherapists across the country during the study, an ideal situation is created for future implementation of the exercise program, if proven effective.

Within the field of exercise-oncology, results can be affected by two features. First, effects of the exercise program in the intervention group might be influenced by adherence. Both non-attendance and non-compliance decrease (exercise) treatment dose, thereby resulting in smaller effect sizes. In order to increase attendance and compliance, we implemented several strategies in our study design. In addition to the short distance to the training facilities, these consist of individual guidance by a trained and experienced physiotherapist, an individualized exercise protocol and regular phone calls with the research team. Though attendance and compliance are important, in studies they are rarely reported [39]. In the present study, attendance and compliance to the supervised exercise program will be strictly registered by the physiotherapist and regularly checked by the researchers, while the documented activities in the exercise log of the participants enable us to calculate compliance with the exercise advice.

Second, effects of the exercise program might be influenced by so-called contamination (non-compliance) of the usual care group. This phenomenon is reported to occur in 37% of exercise-oncology trials and is caused by the fact that patients who participate in these type of trials are often highly motivated to exercise, which subsequently leads to an increase of physical activity levels, not only in patients randomized to the intervention group, but also in those randomized to the usual care group [40]. To prevent contamination, we include physically inactive patients (i.e., they might have less natural preference to adapt high physical activity levels when randomized to usual care), elaborate on the randomized design during the informed consent procedure in order to avoid disappointment when being randomized to the usual care group, and repeatedly stress the importance of the usual care group during the inclusion period. After completion of the trial, patients who were randomized to the usual care group can ask the study team for an exercise advice.

In conclusion, the PERFECT study is the first study to investigate effects of an exercise program in esophageal cancer patients after surgery. As the design closely resembles daily practice, results of this study can contribute both to evidence on effects of exercise in esophageal cancer patients, and potential implementation strategies.

## Abbreviations

CPET: Cardiopulmonary exercise testing
EORTC-QLQ-C30: European Organisation for Research and Treatment of Cancer Quality of Life Questionnaire C30
HRQoL: Health-related quality of life
HRR: Heart rate reserve
MFI: Multidimensional Fatigue Inventory
PERFECT: Physical ExeRcise Following Esophageal Cancer Treatment
RM: Repetition maximum
RPM: Revolutions per minute
VO_2peak_: Peak oxygen uptake
